More recently, polymerase chain reaction (PCR) demonstrated the potential to produce rapid, sensitive and specific results, and is now considered the method of choice for direct pathogen detection. (8) However, there is justified concern when the PCR assay is used as the sole means of detection without culture, serology, or clinical data, because surveillance studies using culture and/or PCR indicate that a prolonged asymptomatic carrier state may occur in some persons. (9-12) Since it is not known whether there is a specific threshold quantity of M. pneumoniae in respiratory tract tissues that can differentiate asymptomatic carrier state from infection, a positive result by PCR may overestimate the clinical importance, and may result in unnecessary use of antibiotics. On the other hand, if quantitative PCR will demonstrate to be a reliable technique for diagnosing M. pneumoniae infection, M. pneumoniae will be diagnosed more often. This will result in more adequate treatment of RTI’s in children. It has been suggested that children colonized with M. pneumoniae might be an unrecognized reservoir for the spread of this pathogen. (12) The application of quantitative PCR assays will be crucial in optimizing diagnosing RTI by M. pneumoniae, and in gaining a better understanding of the carrier state associated with M. pneumoniae. Therefore, this is one of the main objectives of our study.

1. M. pneumoniae is thought to be a pathogen that causes pneumonia in children aged 5 years and older. Choice of treatment is based on this supposed age-distribution. Since M. pneumoniae is not susceptible to β-lactam antibiotics, a macrolide antibiotic is the first choice treatment in this age-group. In children younger than 5 years, β-lactam antibiotics are the first choice treatment, because M. pneumoniae is presumed to be a rare cause of RTI in this age-group. However, data on age distribution are conflicting. (13) Specialized diagnostic techniques showed that M pneumoniae might have a more important role in causing both upper and lower respiratory tract infections than previously thought; they seem to be frequent also in children aged less than 5 years. (4, 14) To address this issue, we will investigate the rate of infection among children belonging to different age groups.

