# STATISTICAL ANALYSIS

Research questions and analysis

Question 1 (objective 1): does asymptomatic carrier state with M. pneumoniae exist (see question 3, we expect to find > 10%, using quantitative PCR) (10), and if so, can asymptomatic carrier state be differentiated from infection using quantitative PCR?

Analysis: in children with respiratory tract infections caused by M. pneumoniae (as defined by positive standard PCR, positive serology, and or positive culture, group A), results from the quantitative PCR (results in copies/ml) will be compared with the results from the quantitative PCR in asymptomatic children (healthy asymptomatic children with positive results from either standard conventional PCR or culture, group B) using the Mann-Whitney U test. A PCR value, which can differentiate asymptomatic carrier state from infection (threshold), will be determined using Receiver Operating Characteristic (ROC) curves. This value should have a high sensitivity and acceptable specificity.

Question 2 (objective 1): what is the sensitivity and specificity of this quantitative PCR?

Analysis: sensitivity and specificity will be determined using Receiver Operating Characteristic (ROC) curves. In addition we will investigate the sensitivity and specificity according to whether the quantitative PCR results in a positive or negative result (lowest possible detecting range is 10 copies).

Question 3 (objective 1): what is the prevalence of asymptomatic carrier state?

Analysis: prevalence of asymptomatic carrier state (a positive result with quantitative PCR) will be calculated in group A (children with a positive quantitative PCR result and RTI not caused by M. pneumoniae) and B (healthy asymptomatic children with a positive PCR result). We expect to find >10% in group B (10).

Question 4 (objective 2): does M. pneumoniae infection occur more often in children older than 5 years?

Analysis: children in group A with a RTI caused by M. pneumoniae will be divided in two groups, according to age (< 5 years and ≥ 5 years) and compared to each other, with respect to the prevalence using 2-test.

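### The carrier-versus-infection PCR threshold is set against healthy carriers only, so its specificity cannot be assumed to hold in children with an RTI who merely carry M. pneumoniae

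*Protocol*

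**What the plan says.** Section 9, Question 1, names both sides of the contrast. The cases are defined "in children with respiratory tract infections caused by M. pneumoniae (as defined by positive standard PCR, positive serology, and or positive culture, group A". The comparators are "healthy asymptomatic children with positive results from either standard conventional PCR or culture, group B". The two are compared with a Mann-Whitney test, and then "A PCR value, which can differentiate asymptomatic carrier state from infection (threshold), will be determined using Receiver Operating Characteristic (ROC) curves".

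Question 2 states that "sensitivity and specificity will be determined using Receiver Operating Characteristic (ROC) curves" and does not name the children without infection. Question 3 recognises a second kind of carrier, "children with a positive quantitative PCR result and RTI not caused by M. pneumoniae", but uses these children only to estimate prevalence.

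The Introduction gives the purpose. It warns that "a positive result by PCR may overestimate the clinical importance, and may result in unnecessary use of antibiotics", and says of a reliable quantitative PCR: "This will result in more adequate treatment of RTI’s in children".

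The ancillary study (Section 12.1.3, Definitions) notes that an RTI child positive by culture or real-time PCR need not have M. pneumoniae disease. It gives the study's gold standard as serology together with standard PCR.

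**The concern.** A healthy child is already distinguished from an infected one by having no symptoms, so no load cut-off is needed there. The cut-off is needed in a child with an RTI and a positive PCR: is M. pneumoniae the cause or a bystander? Question 1 never tests the threshold on bystander carriers with an RTI.

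If their load differs from that of healthy carriers, the reported specificity will be wrong for the children in whom the test would be used. If their load is higher, bystanders would be labelled as infected, which is the unnecessary antibiotic use that the Introduction hopes to avoid. The threshold belongs to objective 1 and to the first main endpoint in Section 7.1.

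**Working it through.** **1. Who enters the analysis**

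| Children | Question 1 | Question 2 | Question 3 |
|---|---|---|---|
| Group A, M. pneumoniae RTI | cases | not named | not carriers |
| Group B, healthy, PCR- or culture-positive | only comparator | not named | carriers |
| Group A, PCR-positive, RTI from another cause | no place as non-cases | not named | carriers |

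The exclusion is explicit for the Question 1 threshold. For Question 2 it is an inference.

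**2. Where RTI carriers go.** Section 3 (Aim I) and Question 1 accept any one of standard PCR, serology or culture. A child with another RTI who carries the organism and is positive by standard PCR or culture is therefore a case. Only a child positive by quantitative PCR and negative on all three other tests is left for Question 3's group A carriers. Section 12.1.3 says that a positive culture or real-time PCR does not by itself mean disease, so the sections conflict.

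**3. How many.** Section 12.1.4 expects 10% of group A to be positive by culture or PCR, and reports about 10% of enrolled children PCR-positive so far. Its own projection reproduces: half of 1,000 children × 10% = 50 further positives. For group A as a whole, 500 × 10% = 50, cases and bystanders together. Adding 10% carriage to the remaining 450 children (45) on top of 50 cases would give 95/500 = 19%, which does not fit the 10%. If 20% or 50% of the 50 positives were bystanders (assumed), there would be 10 or 25.

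**4. Effect on specificity (illustration; all loads assumed).** Take normal log loads with equal SD, and RTI carriers shifted by d SD from healthy carriers. A threshold with 80% specificity in healthy carriers then has specificity Φ(Φ⁻¹(0.80) − d) = Φ(0.842 − d) in RTI carriers:

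| d | −0.25 | 0 | 0.25 | 0.5 | 0.75 |
|---|---|---|---|---|---|
| Specificity | 86% | 80% | 72% | 63% | 54% |

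Alternatively, set the threshold for 90% sensitivity with infected children 2 SD above healthy carriers: t = 2 − 1.282 = 0.718. Specificity is Φ(0.718) = 76% in healthy carriers. In RTI carriers it is Φ(0.718 − d) = 68%, 59% or 49% for d = 0.25, 0.5 or 0.75.

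**5. Effect of counting bystanders as cases (same model, d = 0.5).** Let a share f of the labelled cases be bystanders. At t = 0.718, apparent sensitivity = (1 − f) × 0.90 + f × (1 − 0.586).
- f = 0.2: 0.720 + 0.083 = 80%.
- f = 0.5: 0.450 + 0.207 = 66%.

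Restoring an apparent 90% at f = 0.2 moves the threshold down to 0.162, since 0.8 × Φ(1.838) + 0.2 × Φ(0.338) = 0.8 × 0.967 + 0.2 × 0.632 = 0.900. Specificity in healthy carriers is then Φ(0.162) = 56% instead of 76%. So the case definition distorts sensitivity and the threshold as well.

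**6. Why the non-cases must be PCR-positive.** PCR-negative children lie below any threshold. With d = 0.5, pooling 450 negatives with 25 bystanders gives (450 + 25 × 0.634)/475 = 98%. Even with 405 negatives and 45 bystanders the result is (405 + 45 × 0.634)/450 = 96%. Both conceal the 63% among carriers.

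**7. Precision.** The approximate 95% half-width at 80% specificity is 1.96 × √(0.16/n): 25 points for n = 10 (where the approximation is crude), 16 for n = 25, and 11 for 50 healthy carriers.

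**The case against.** The strongest reply is that Question 1 does what the objective literally asks, namely to separate asymptomatic colonization from infection. The Summary calls the study explorative, and no treatment within it depends on the threshold. That stands, and it lowers the weight of the point. It does not bridge the gap between the comparator and the use described in the Introduction.

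Second, Question 2 may intend a wider population. It also plans sensitivity and specificity for a simple positive or negative quantitative PCR, which would say little among children already selected as positive. This stands too: the population of Question 2 is unstated and should not be described as healthy carriers only.

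Third, a reader might infer that all RTI carriers are simply left out, and that about 45 of them are missing beside 50 cases. The documents support neither. Under the any-test rule most would be counted as cases, and total positivity of about 10% leaves room for about 50 positives altogether.

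Fourth, a reader might infer that specificity is certainly overstated. The Introduction says only that viral damage might facilitate infection with M. pneumoniae, and that almost nothing is known about this. It does not say that load rises in bystander carriers, so the error could go either way.

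**Conclusion.** The point holds in limited form. Question 1 derives the threshold from a contrast that omits, as non-cases, the carriers among whom the clinical question arises. Its specificity therefore cannot be assumed to apply to children with an RTI.

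The size and direction of the error are unknown. The illustrated range, from 86% down to 54% against a nominal 80%, rests wholly on assumed normal loads and shifts of −0.25 to 0.75 SD. If the load distributions of the two carrier groups match, there is no error from this source. The conflict over what counts as infection is a firm finding that needs no assumption. It affects the cases, while the choice of comparator would remain a problem even under a perfect reference standard.

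This should be corrected before analysis. In an explorative study it is not a defect that invalidates the design.

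**What to change.** 1. Reconcile Section 3 (Aim I), Section 9 (Question 1) and Section 12.1.3 into one serology-based reference standard under which a positive PCR alone does not make a case. State how a positive culture alone is classified.
2. In Questions 1 and 2, add a ROC curve and a specificity estimate whose non-cases are group A children who are PCR-positive and whose RTI is not attributed to M. pneumoniae. Do not pool PCR-negative children into this estimate.
3. Keep the comparison with healthy group B carriers as a separate, clearly labelled estimate, and name the non-infected population wherever Question 2 reports specificity.
4. Limit conclusions about diagnosing children with an RTI to the group A estimate, reported with its confidence interval.

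The cost is wording and one further analysis. The swabs, lavages and paired group A sera are already planned, and no extra children are needed. The downsides are real: the group A non-cases may be few, their specificity imprecise or less favourable, and children who miss the second visit will lack a paired serum, so their number should be reported.

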# STUDY POPULATION

## Population (base)

Age: 0-16 years

Group A: 500 children visiting the Emergency Department/HAP because of upper or lower respiratory tract infection, from which: 400 children <5 years and 100 children ≥ 5 years.

Group B: 500 healthy controls; recruited from children attending the outpatient clinic in preparation of their surgery. Again: 400 children <5 years and 100 children ≥ 5 years.

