## Sample size calculation

For estimated group sizes in 2 years of 500 in group A and 500 in group B small differences in mean quantitative result of PCR will be demonstrable (α = 0.05, power ≥ 90%) if the effect-size (difference of mean/standard deviation) is 0.20 or larger, which can be considered as a small difference. Group A we aim to include pre-calculated numbers according to age (400 children, < 5 years, versus 100 children, > 5 years). Because of a high prevalence viral RTI below 5 years of age, it is necessary to include more children with RTI in this group, to find a reasonable number of M. pneumoniae infections. Assuming up to 10% M. pneumoniae infections below 5 years of age we will be able to detect a 12% difference using these numbers in these subgroups (< 5 years versus >5 years). For comparison we aim to include the same numbers in group B (healthy children).

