### Study population

## *Population*

Group A+/HAP+: children, aged 0-16 years tested positive for *M. pneumoniae* in group A/HAP by culture or PCR (we expect to find 10% *M. pneumoniae* positive RTI).

Group B+: children, aged 0-16 years tested positive for *M. pneumoniae* in group B by PCR or culture (we expect to find 10% of these children to be positive by PCR).

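### The PCR threshold is chosen on the study's own ROC curve by an open criterion and its accuracy is read from the same enrolled children, so that accuracy is expected to be modestly too high

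*Protocol*

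**What the plan says.** Protocol section 9 (Statistical analysis), Question 1, compares quantitative PCR results in group A children whose respiratory infection is attributed to M. pneumoniae with those in group B children who are positive by conventional PCR or culture. A threshold separating carriage from infection is then derived from ROC curves. The guidance on choosing it is: "This value should have a high sensitivity and acceptable specificity".

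Question 2 asks for the sensitivity and specificity of the quantitative PCR and answers that "sensitivity and specificity will be determined using Receiver Operating Characteristic (ROC) curves". It adds a second analysis by positive or negative result, with a detection limit of 10 copies. It does not say which children enter either analysis.

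Section 4.1 describes a single sample: "Group A: 500 children visiting the Emergency Department/HAP because of upper or lower respiratory tract infection" and "Group B: 500 healthy controls; recruited from children attending the outpatient clinic in preparation of their surgery". The protocol mentions no separate validation sample, sample split, cross-validation or bootstrap correction. On expected positives, section 12.1.4 says of group A "we expect to find 10% *M. pneumoniae* positive RTI" and of group B "we expect to find 10% of these children to be positive by PCR". Section 9, Question 3, expects more than 10% carriers in group B.

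**The concern.** A cut-off picked because it performs well in a sample partly fits the chance features of that sample. Sensitivity and specificity read at that cut-off in the same children are then, on average, better than the cut-off would achieve in new children. Two features of the plan matter here. The criterion is two adjectives without numbers, so the choice can be made after the curve has been seen. And Question 1 uses only M. pneumoniae-positive children, a small part of the 1,000 enrolled.

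Telling colonization from infection by quantitative PCR is objective 1 and the first main endpoint (section 7.1). Section 1 links it to antibiotic use. If the accuracy of the threshold is reported too favourably, that is the use that would be misled.

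**Working it through.** **The plan's own figure.** The protocol gives no figure for threshold accuracy or for the size of the ROC sample. Its only related figure is the power statement in section 4.4: "α = 0.05, power ≥ 90%) if the effect-size (difference of mean/standard deviation) is 0.20 or larger". With 500 per group and a two-sided test:

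power = Φ(d·√(n/2) − 1.96) = Φ(0.20 × 15.81 − 1.96) = Φ(1.20) = 88.5%.

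One-sided it is 93.5% (sidedness is not stated). Exactly 90% two-sided needs 526 per group, and the effect detectable with 500 is 0.205. The stated figure is reproduced to within rounding and is not at issue. It concerns a comparison of all 500 with all 500, so it says nothing about a threshold set in the positive children.

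**Size of the ROC sample (inferred).**
- Group A: 0.10 × 500 = 50.
- Group B: 0.10 × 500 = 50, or more, since Question 3 expects over 10%.
- Using the age assumptions of section 4.4 for group A (10% under 5 years, and 10% + 12% = 22% from 5 years): 0.10 × 400 + 0.22 × 100 = 40 + 22 = 62.

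**Size of the bias.** The protocol gives no load distribution. Log load is therefore assumed normal with equal variance in both groups, separated by √2·Φ⁻¹(AUC). In each of 4,000 simulated data sets per setting, a cut-off is selected on the sample. Its apparent sensitivity (Se) and specificity (Sp) are compared with the true values at that cut-off. Two rules are tried because the protocol fixes neither: the maximum of Se + Sp, and the highest Sp with Se of at least 90%. Results for 50 vs 50, in % (differences taken before rounding):

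| True AUC | Rule | Apparent Se / Sp | True Se / Sp | Excess Se / Sp (points) |
|---|---|---|---|---|
| 0.7 | max Se + Sp | 70.3 / 65.7 | 65.0 / 61.8 | 5.3 / 3.9 |
| 0.8 | max Se + Sp | 77.4 / 73.3 | 72.9 / 69.9 | 4.5 / 3.4 |
| 0.9 | max Se + Sp | 85.5 / 82.9 | 81.6 / 80.2 | 3.9 / 2.8 |
| 0.7 | Se ≥ 90% | 91.0 / 32.1 | 88.5 / 31.6 | 2.5 / 0.5 |
| 0.8 | Se ≥ 90% | 90.8 / 48.8 | 88.5 / 48.4 | 2.3 / 0.4 |
| 0.9 | Se ≥ 90% | 90.9 / 71.8 | 88.6 / 71.2 | 2.3 / 0.6 |

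**Dependence on sample size** (max Se + Sp; excess in the sum of the two, AUC 0.7 to 0.9):
- 25 vs 25: 10.0 to 13.4 points
- 50 vs 50: 6.7 to 9.2 points
- 62 vs 50: 6.3 to 8.9 points
- 500 vs 500: 1.6 to 2.4 points

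The small number of positive children is what makes the bias noticeable.

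**If Question 2 also uses PCR-negative children.** With 50 infected children against an assumed 450 or 950 others, the specificity excess is at most 0.6 points. The sum is 5 to 7 points under max Se + Sp and about 2 points under the sensitivity floor. The reduction is in specificity: under max Se + Sp, nearly all of what remains is in sensitivity.

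**Scale against sampling error.** For 45 of 50 (90%), the exact 95% interval is 78% to 97%, which is wider than any of the biases at 50 vs 50.

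**The case against.** The strongest reply is that this belongs in a statistical analysis plan, which is not shown. The protocol fixes the comparison, the test, the ROC method and a priority (sensitivity first). A numeric floor and a bootstrap are details that could follow. The study also calls itself explorative in its Summary, and section 9 does not claim that the threshold is validated. Part of this stands: the point is moderate, and an unseen plan could repair it. But section 9 does set out the procedure. Followed as written, it gives accuracy that is too high on average, so this is more than a missing detail.

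Three stronger readings are tempting, and the documents do not support them.

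- A reader might infer that accuracy will be overstated by 7 to 10 points. That is the sum of two measures, and it applies only if the cut-off maximises that sum. The protocol states no such rule, and its wording is closer to a sensitivity floor, where the sum is about 3 points. It is also an average bias and need not appear in a given data set.
- A reader might infer that the protocol evaluates the threshold in exactly the same 50 vs 50 children. That number is inferred, and Question 2 names no population. Its positive-or-negative analysis needs PCR-negative children as well. What the protocol does support is that no children outside the enrolled sample are available.
- A reader might infer that every accuracy figure is affected. The 10-copy analysis has a cut-off fixed in advance, so selection cannot bias it. The empirical AUC of one unfitted marker does not depend on the cut-off and needs no optimism correction.

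**Conclusion.** The point holds in a limited form. Sensitivity and specificity at the ROC-selected threshold are expected to be too high, because selection and assessment use the same enrolled sample without correction.

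The expected excess is about 3 to 5 points in each measure if the cut-off maximises their sum. With a 90% sensitivity floor it is about 2 to 3 points in sensitivity and under 1 point in specificity. These figures rest on about 50 positive children per group, binormal loads of equal variance and AUC 0.7 to 0.9. The first two are an inference and an assumption, and the protocol gives no AUC. Fewer positives would enlarge the excess. That is possible, because section 12.1.3 describes a stricter reference standard (serology together with standard PCR) than section 9 does. Including PCR-negative children would shrink the total.

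The bias is smaller than the sampling error, so it does not undermine the study. It is worth correcting because it runs in one direction, concerns the main product of objective 1 and is cheap to remove.

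**What to change.** 1. State a numeric selection rule in section 9 now, before any further analysis of bacterial load; for example, the highest specificity among cut-offs with sensitivity of at least 90%. The timing cannot be tied to unmasking: section 7.2 makes blinding not applicable, and section 12.1.1 reports that preliminary loads in patients and healthy children have already been compared.
2. State which children enter the sensitivity and specificity analysis in Question 2.
3. Report sensitivity and specificity at the chosen threshold corrected by a bootstrap that repeats the cut-off selection in each resample. In simulation under the assumptions above, this removed most of the bias.
4. Give 95% intervals for the corrected sensitivity and specificity, for the threshold and for the AUC. The AUC itself stays uncorrected.
5. Describe the threshold as needing validation in independent children.

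The cost is a little more analysis and slightly less favourable reported accuracy. No additional child, sample or visit is needed.

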**SUMMARY**

Rationale

150 million children/year suffer from pneumonia worldwide, and 20 million children have to be hospitalized for this reason. Up to 40% of community-acquired pneumonias are caused by Mycoplasma pneumoniae and as many as 34% of cases requiring hospitalization in children. Studies using the recently introduced PCR suggest that M. pneumoniae frequently causes respiratory tract infections (RTI), not only in older children as previously thought, but also in children younger than 5 years. This is important because M. pneumoniae is not sensitive to the first choice β-lactam antibiotics. Moreover, it is unknown whether the detection of M. pneumoniae by PCR also confirms this pathogen as the cause of the infection. A limited number of studies suggest the existence of an asymptomatic carrier state. Due to the shortcomings in diagnosis, knowledge on the role of different host- and bacterial factors on progression to infection is very limited.

Hypothesis

M. pneumoniae is capable of asymptomatic colonization, which can be differentiated from infection by quantitative PCR. M. pneumoniae causes RTI’s in children younger than 5 years as frequently as in older children. The genetic background of M. pneumoniae strains as well as viral co-infections influence progression from colonization to infection.

Objectives

1. To optimize the diagnosis of M. pneumoniae infections by discriminating between colonization and symptomatic infection using quantitative PCR.

2. To study the role of host factors (age, and bacterial and viral co-infection) on infection by M. pneumoniae.

3. To investigate the relationship between M. pneumoniae genotype and virulence.

Study design

Prospective design

Study population

Group A: children with a suspected RTI

Group B: healthy controls

Intervention

Not Applicable.

Main study parameters/endpoints

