Below five years of age there’s a high prevalence of viral infections. It is therefore necessary to use a greater number of children with RTI in that group to find a reasonable number of M. pneumoniae infections. Using a pre-calculated number of children < 5 years (400) and > 5 years (100), the detectable difference will be 12 % assuming prevalence up to 10% in the < 5 years of age group.

Question 5 (objective 2): do children with M. pneumoniae and a viral or bacterial co-infection have more severe illness?

Analysis: children in group A with a RTI caused by M. pneumoniae will be divided in two groups: children without co-infection, and children with a viral or bacterial co-infection. Severity of disease will be scored according to diagnosis, severity of respiratory distress (days of required oxygen or mechanical ventilation and days of hospitalization. Groups will be compared using Mann-Whitney U test.

Question 6 (objective 3): does genotype of M. pneumoniae influence the rate of asymptomatic carrier state (level of PCR in healthy children, group B), and/or severity of disease?

Analysis: depending on the number of different genotypes of M. pneumoniae found, we will compare these different genotypes to PCR levels using Kruskal-Wallis test. This will be done in the asymptomatic children (healthy M. pneumoniae carrierstate) as well as the children with a M. pneumoniae RTI. Severity of disease will be scored according to severity of respiratory distress (days of required oxygen or mechanical ventilation) and days of hospitalization. This will be compared with different genotype by Kruskal-Wallis test in the symptomatic group (children with M. pneumoniae RTI).

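### The Summary hypothesises equal infection frequency under and over 5 years, but Question 4 fixes only a test of difference, whose non-significant result could be taken as support

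*Protocol*

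**What the plan says.** The Summary, under Hypothesis, holds that M. pneumoniae causes respiratory tract infection "in children younger than 5 years as frequently as in older children". This is a statement of equal frequency.

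The Statistical Analysis section links Question 4 to objective 2 and asks "does M. pneumoniae infection occur more often in children older than 5 years". Group A children with an M. pneumoniae infection are split at 5 years and "compared to each other, with respect to the prevalence using" a chi-square test (the Greek letter was lost when the text was extracted). Neither a margin nor an interval criterion is given for this comparison, and the protocol does not say how a non-significant result is to be read.

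The Population section sets the numbers in group A: "400 children <5 years and 100 children ≥ 5 years". The Sample size calculation takes a base rate of at most 10% in the younger group and gives the planning figure: "we will be able to detect a 12% difference using these numbers in these subgroups". Question 4 repeats it: "the detectable difference will be 12 % assuming prevalence up to 10% in the < 5 years of age group". No power and no sidedness is stated for the age comparison.

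**The concern.** The hypothesis and the test point in opposite directions. If the hypothesis is true, the expected outcome of the chi-square test is non-significance. Non-significance is also a likely outcome when older children have a clearly higher rate, because the older group has only 100 children and the comparison is planned around a difference that more than doubles the base rate (10% to 22%). The planned result therefore cannot separate similar frequency from too little information.

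This matters for objective 2. Age distribution is listed among the main endpoints, and the Introduction gives as the reason for the age question that first-choice antibiotic treatment currently follows a presumed age pattern. A reader of the results will want to know whether a null finding means the rates are close.

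**Working it through.** **Inputs.** n1 = 400 (under 5) and n2 = 100 (5 and over), from Population. Base rate p1 = 10%, from Sample size calculation; the protocol gives it as a ceiling. Detectable difference 12 points, from Sample size calculation and Question 4. Assumption: α = 0.05, two-sided unless noted, because the protocol does not state it for this comparison.

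**Formulas.** With p̄ = (400·p1 + 100·p2)/500:
- SE0 = √[p̄(1−p̄)(1/400 + 1/100)]
- SE1 = √[p1(1−p1)/400 + p2(1−p2)/100]
- power = Φ[(p2 − p1 − z·SE0)/SE1], with z = 1.96 two-sided or 1.645 one-sided

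**Step 1: the plan's own figure, 10% against 22%.**
- p̄ = 0.124, SE0 = √(0.108624 × 0.0125) = 0.03685, SE1 = √(0.000225 + 0.001716) = 0.04406.
- One-sided: (0.12 − 0.0606)/0.04406 = 1.348, power 91% (92% by exact binomial enumeration).
- Two-sided: (0.12 − 0.0722)/0.04406 = 1.084, power 86%.
- Solving for the detectable difference gives 11.7 points (one-sided, 90% power), about 11.75 (two-sided, 80%, continuity-corrected), 12.4 (two-sided, 80%, unpooled) and 13.0 (two-sided, 90%, pooled).

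Standard variants therefore reproduce 12 points, and the figure is not an error.

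**Step 2: how often the test is non-significant when the rates truly differ (two-sided).**
- 10% against 16%: p̄ = 0.112, SE0 = 0.03526, SE1 = 0.03961; (0.06 − 0.06911)/0.03961 = −0.230, power 0.41, non-significant 59%.
- 10% against 18%: p̄ = 0.116, SE0 = 0.03580, SE1 = 0.04124; (0.08 − 0.07017)/0.04124 = 0.238, power 0.59, non-significant about 40% (0.405 by exact enumeration).
- By exact enumeration, non-significance is 69% at 10% against 15%, and about 25% at 10% against 20%, a doubling.

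If the test were one-sided:
- 16%: (0.06 − 0.0580)/0.03961 = 0.050, non-significant about 48%.
- 18%: (0.08 − 0.0589)/0.04124 = 0.512, non-significant about 30%.

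The point does not depend on sidedness.

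**Step 3: one possible data set.** With 40/400 (10%) against 16/100 (16%), chi-square = 500 × (40×84 − 360×16)² / (400 × 100 × 56 × 444) = 2.90. This is below 3.84 and so not significant. The 95% interval is 6.0 ± 1.96 × 3.96, or −1.8 to 13.8 points. The interval shows that a large excess in older children remains possible; the bare test does not.

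**Step 4: precision if the rates are equal at 10%.** SE = √[0.09 × (1/400 + 1/100)] = 0.0335, so the 95% half-width is 1.96 × 3.35 = 6.6 points.

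**Step 5: would 12 points serve as a margin?** Take the rule that frequency counts as equal if the 95% upper limit (Wald) is below 12 points, with 10% under 5. By exact enumeration the rule is met 91% of the time when the rates are equal. It is also met 57% of the time at a true 14% in older children, 46% at 15%, 36% at 16% and 19% at 18%. A 12-point margin would often endorse the conclusion it is meant to guard against.

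**The case against.** The strongest reply is that Question 4 is worded as a question about a difference, and a chi-square test fits that wording. The equality statement is one sentence in the Summary of a study that calls itself explorative. Elsewhere the age aim is descriptive: rates by age group and age distribution. A confidence interval and a sentence on interpretation are often left to the statistical analysis plan, and the protocol attaches no treatment rule to the answer.

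Much of this stands, and it limits the weight of the point. It does not remove the mismatch, because the hypothesis, the question, the test and the planning figure are all fixed in this protocol and do not fit together.

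Two stronger readings are tempting, and the document does not support them.
- A reader might infer that the investigators intend to treat non-significance as confirmation. The protocol never says so; it could be read that way, and no more can be claimed.
- A reader might infer that 12 points misses a promised 90% power. The statement "α = 0.05, power ≥ 90" percent belongs to the comparison of mean PCR results in 500 against 500 children. The age comparison has no stated power or sidedness, and Step 1 reproduces 12 points.

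**Conclusion.** The point holds as a mismatch between hypothesis and analysis. The chi-square test can refute equal frequency but cannot support it. With 400 and 100 children and 10% under 5, a 1.6-fold higher rate in older children would be missed about 59% of the time and a 1.8-fold higher rate about 40% of the time (two-sided 0.05; about 48% and 30% one-sided). These figures assume that the planned numbers are reached and that the rate under 5 is 10%, the top of the protocol's assumption. The 12-point planning figure stands. Because the study is exploratory, the correction is worth making but does not threaten the design.

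**What to change.** In Question 4, make the main result the prevalence difference (5 years and over minus under 5) with its 95% confidence interval, reported alongside the chi-square test. State that a non-significant test is not evidence of equal frequency.

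Then bring the Summary into line in one of two ways:
- restate the age hypothesis as a difference or estimation question; or
- keep it, and limit any conclusion of similar frequency to the differences that the interval excludes.

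If a margin is used, the sponsor should justify it in advance. The 12-point detectable difference should not become the margin by default (Step 5).

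The cost is a few sentences and one interval, with no added recruitment. The downside is that any claim of similar frequency is limited by the width of the interval, about ±6.6 points if both rates are 10%.
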